## Abstract

**Background:**

Postprandial distress syndrome (PDS) is referred to as meal-related functional dyspepsia (FD) and causes a reduced quality of life (QoL) for patients. Several randomized controlled trials (RCTs) have suggested that acupuncture is an effective treatment for FD, but few studies were particularly for PDS. This pilot study was designed to determine the feasibility and efficacy of acupuncture in patients with PDS characterized by postprandial fullness and early satiation according to the Rome III criteria.

**Methods:**

This is a multi-center, two-arm, blinded (participants), pilot RCT. Forty-two participants who meet the inclusion criteria will be randomly assigned to the verum acupuncture group or minimal acupuncture group in a 1:1 ratio. Both treatments consist of 12 sessions of 20 min duration over four weeks (three sessions per week). The primary outcome measurement is the proportion of persons who improve as assessed using the global outcome by the overall treatment effect (OTE) at end-of-treatment (EOT) (four weeks after randomization). Global assessment at weeks 8 and 16 after randomization is one of the secondary outcomes. The other secondary outcomes including symptoms, disease-specific QoL, and depression and anxiety will be assessed at weeks 4, 8, and 16 after randomization.

**Discussion:**

This pilot study will help determine the feasibility and efficacy of acupuncture in patients with PDS.

**Trial registration:**

ISRCTN Registry, ISRCTN18135146. Registered on 7 July 2016.

**Electronic supplementary material:**

The online version of this article (doi:10.1186/s13063-017-2285-9) contains supplementary material, which is available to authorized users.

## Background

Functional dyspepsia (FD) is classified into postprandial distress syndrome (PDS) and epigastric pain syndrome (EPS) based on accumulating epidemiological and pathophysiological data [1, 2]. PDS is a characterized by postprandial fullness and early satiation [2], in the absence of any organic, systemic, or metabolic disease that likely explains the symptoms. Both in the general population and in patients, the most common symptom is postprandial fullness (68–86%)—the main symptom of PDS [3, 4]. PDS might have a higher prevalence of impaired gastric accommodation than EPS [1]. Only a few randomized controlled trials (RCTs) were conducted to examine the treatment responses of PDS and EPS, though testing responses to different FD subgroup are urgently needed [1].

This condition is not a life-threatening disease [5, 6], although patients suffer from a reduced quality of life (QoL) [7–11]. According to a ten-year follow-up study, up to 40% of people with the condition consult a primary care physician [12]. PDS is associated with higher rates of absenteeism and lower productivity at work [13, 14]. Employed people with dyspepsia possibly have a reduced potential productivity of 35.7% [15]. In the United States, costs associated with FD in 2009 were in excess of US$18 billion, meaning that it has substantial financial implications for patients, healthcare organizations, and society [16, 17].

Given the limited efficacy of the major of current treatments for FD, it is not surprising that alternative therapies including acupuncture are attractive to both patients and practitioners [18, 19]. Several RCTs have suggested that acupuncture is an effective treatment for FD [19–21]; however, the studies designed especially for PDS with acupuncture treatment were few. Only a retrospective analysis of acupuncture for FD showed that PDS patients responded better to the acupuncture therapies compared with EPS [22] and acupuncture was not more effective in epigastric pain and epigastric burning (the main symptoms of EPS) than sham acupuncture [23]. The differences in pathological mechanisms of PDS and EPS have been controversial and it remained indistinct whether different treatments are needed for EPS and PDS [1]. Therefore, further RCTs to evaluate the treatment responses of PDS are needed. We designed this study to determine the feasibility and efficacy of acupuncture in patients with PDS.

## Methods/Design

### Study design

Figure 1 shows the study design. This multi-center, two-arm, blinded (participants), pilot RCT will be conducted at three centers: Beijing Hospital of Traditional Chinese Medicine Affiliated to Capital Medical University; Dongzhimen Hospital Affiliated to Beijing University of Chinese Medicine; and Beijing Friendship Hospital Affiliated to Capital Medical University in China. The participants will be recruited primarily through advertisements on hospital social media, general practitioners, and public community service centers. This trial was registered with ISRCTN at Current Controlled Trials (ISRCTN18135146, Additional file 1) and followed the Declaration of Helsinki Good Clinical Practice guidelines for trial conduct. The study protocol (version 1.0, 18 January 2016) has been approved by the Research Ethics Committee of Beijing Hospital of Traditional Chinese Medicine Affiliated to Capital Medical University (reference: 2016BL-011-01) and conformed to CONSORT [24] and STRICTA guidelines [25] for acupuncture studies (Additional file 2). Before randomization, all participants will be requested to provide written informed consent.

**Fig. 1 Fig1:**
[figure not shown]
*Flowchart* of trial procedures

### Eligibility

#### Inclusion criteria

Aged 18–65 years (either sex)Meeting the Rome III PDS criteriaNormal esophagogastroduodenoscopy results within one yearNo other treatments received during the studyWilling to sign written informed consent

#### Exclusion criteria

Presence of serious structural disease (disease of heart, lung, liver, or kidney)Signs of irritable bowel syndromeSurgery related with the gastrointestinal tractSevere coagulopathyTaking drugs that might affect dyspepsia, such as anti-secretary drugs, antacids, prokinetics, non-steroidal anti-inflammatory drugs, and antidepressants two weeks before participating in the trialDifficulties in attending the trial, such as serious mental illness, dementia, or illiteracyDrug or alcohol abusePregnant or breastfeeding

#### Randomization and allocation concealment

All participants who meet the inclusion criteria will be randomly assigned to the verum acupuncture group or minimal acupuncture group in a 1:1 ratio according to a randomization sequence generated using SPSS19.0 software. The randomization sequence will be prepared by a professional statistician, who will not be involved in assessment or treatment of participants. An independent clinical trials researcher will implement the allocation schedule using a centralized telephone randomization procedure. The random number will be assigned after the participants have met all inclusion criteria and completed baseline assessment. The Clinical Research Coordinator (CRC) will be responsible for enrolling participants, obtaining informed consent and requesting randomization.

#### Blinding

The acupuncturists who deliver the treatment to the participants will not be blind to treatment allocation. Blinding of acupuncturists is not possible due to the nature of acupuncture. Participants and all other investigators will be blinded to the treatment allocation, including the data analysis and outcome assessors. Treatment groups will be identified as Group A and Group B during the statistical analysis of all the data for data analysis.

#### Intervention

The treatment protocol for acupuncture was developed using the clinical experience of acupuncture experts for reference. Verum acupuncture and minimal acupuncture will be performed by certified acupuncturists who hold a Chinese medicine practitioner license from the Ministry of Health of the People’s Republic of China and worked for at least three years in clinics. Before the trial, all the acupuncturists will be required to take special training to acquire a full understanding of the performance of treatment and receive a brochure showing detailed information on the standardized operation. The training included the method of the location of acupoints and non-acupoints as well as manipulation of acupuncture and minimal acupuncture. We will use sterile needles (Huatuo disposable acupuncture needle) in sizes of 0.25 × 25 mm or 0.25 × 40 mm. Both the verum acupuncture and minimal acupuncture treatments consist of 12 sessions of 20 min duration over four weeks (three sessions per week). The use of other treatments related to PDS, such as prokinetic agents or tricyclic antidepressants, will not be allowed.

#### Verum acupuncture

Participants randomized to the verum acupuncture group will undergo treatment lying down with needles inserted at the selected acupuncture points. Table 1 and Fig. 2 describe the verum acupuncture point prescription. Acupuncturists will be required to achieve the typical acupuncture sensation of De qi and needles will be stimulated manually for at least 30 s at every acupoint and retained in place for 20 min. De qi, literally meaning “arrival of energy,” is referred to as a sensation of numbness or distension and may be one indication that acupuncture is exerting its beneficial effects.

**Table 1 Tab1:** Location of acupoints in verum acupuncture group

Acupoints	Location
Baihui (DU20)	On the midline of the head, 7 cun^a^ directly above the midpoint of the posterior hairline
Zhongwan (RN12)	On the anterior midline, 4 cun above the umbilicus
Tianshu (ST25)	On the same level of the umbilicus and 2 cun lateral to the anterior midline
Qihai (RN6)	On the anterior midline, 1.5 cun below the umbilicus
Neiguan (PC6)	On the line joining Daling and Quze, between the tendons of palmaris longus and flexor carpi radialis, 2 cun above the transverse crease of the wrist
Danzhong (RN17)	On the anterior midline, on the level of the fourth intercostal space, at the midpoint of the line joining the two nipples
Zusanli (ST36)	3 cun directly below Dubi (ST35) and one finger-breadth lateral to the anterior border of the tibia
Gongsun (SP4)	On the medial side of the foot, in the depression anterior and inferior to the first metatarsal bone, at the junction of the red and white skin

^a^One “cun” is defined as the width of the interphalangeal joint of patient’s thumb

**Fig. 2 Fig2:**
[figure not shown]
Location of acupoints in verum acupuncture group

#### Minimal acupuncture

Non-acupoints with a superficial puncture (2 mm in depth) will be performed in minimal acupuncture group, without considering a needle sensation and manual stimulation. The locations of non-acupoints are away from any acupoints or meridians and shown in Table 2 and Fig. 3. The treatment disposal will be the same as in the verum acupuncture group.

**Table 2 Tab2:** Location of non-acupoints in minimal acupuncture group

Non-acupoints	Location
NP1	In the middle of Jiaosun (SJ20) and Shuaigu (GB8) points
NP2	2.0 cun^a^ above the anterior superior iliac spine
NP3	2.0 cun below the umbilicus and 1.0 cun lateral to the anterior midline
NP4	In the middle of the medial epicondyle of the humerus and the styloid process of ulna
NP5	3.0 cun below Yanglingquan (GB34), between the gallbladder and bladder meridian
NP6	In the middle of Qiuxu (GB40) and Jiexi (ST41) points

^a^One “cun” is defined as the width of the interphalangeal joint of patient’s thumb

**Fig. 3 Fig3:**
[figure not shown]
Location of non-acupoints in minimal acupuncture group

#### Outcomes

Table 3 summarizes the outcomes and the time-points of data collection during the trial.

**Table 3 Tab3:** Time to visit and data collection

Outcomes	Baseline	Treatment				Follow-up		
		1 weeks	2 weeks	3 weeks	4 weeks	8 weeks	12 weeks	16 weeks
Patients								
Informed consent	×							
Screening	×							
Sign informed consent	×							
Randomization	×							
Primary outcome								
OTE					×			
Second outcome								
OTE		×	×	×		×	×	×
Symptoms	×	×	×	×	×	×	×	×
NPI	×				×	×		×
HADS	×				×	×		×
Adverse events		×	×	×	×			

*OTE* overall treatment effect, *NPI* Nepean Dyspepsia Index, *HADS* Hospital Anxiety Depression Scale

#### Primary outcome measurement

The primary outcome is the responder rate based on the overall treatment effect (OTE) at end-of-treatment (EOT, four weeks after randomization) [26, 27]. The patient will be asked to decide whether symptoms have changed compared with pre-treatment using a Likert scale. The question will be asked “How were your gastric symptoms during the past week in comparison with the baseline period?” The seven-point Likert scale consists of “extremely improved,” “improved,” “slightly improved,” “not changed,” “slightly aggravated,” “aggravated,” and “extremely aggravated” [27]. Patients who are “extremely improved” or “improved” of the OTE will be considered responders. OTE has been used as the primary and secondary outcomes measure in several trials with FD [27–31]. The advantage of this endpoint is that it closely resembles the way physicians evaluate treatment benefit in clinical practice, but the main disadvantage is the inherent recall of pre-treatment symptom severity which may lead to bias [26].

### Secondary outcome measurements

#### Global assessment at other time-points

The primary outcome measurement is the OTE at the EOT; however, responder rate based on OTE will also be measured weekly (during the treatment) and at weeks 8, 12, and 16 after randomization with a seven-point Likert scale [27].

#### Symptoms assessment

The eight dyspepsia symptoms including postprandial fullness, early satiation, upper abdominal bloating, epigastric pain, epigastric burning, nausea, vomit, and belching will be assessed at baseline, once a week for four weeks in the treatment period and at weeks 8, 12, and 16 after randomization. The severity of each symptom is rated as a four-item questionnaire: asymptomatic (0 points); mild (1 point); moderate (2 points); or severe (3 points) [20]. A higher score reflects a more serious disease state.

#### Disease-specific QoL assessment

QoL will be assessed at baseline and at weeks 4, 8, and 16 after randomization using the 25-item Nepean Dyspepsia Index (NDI) [32–34], which measures the specific life quality of FD patients in four domains: interference (13 items); know/control (seven items); eat/drink (three items); and sleep/disturb (two items). The scores are measured using a five-point Likert scale that ranges from “not at all” to “extremely,” with higher scores indicating a better QoL.

#### Depression and anxiety assessment

Depression and anxiety symptoms will be assessed by the Hospital Anxiety Depression Scale (HADS), which has been validated for in a wide variety of general medical patients. It is a self-report inventory consisting of 14 questions, seven of which relate to anxiety symptoms and seven to depressive symptoms. A higher score reflects a more serious state of depression and anxiety. The participants will complete the HADS at baseline and at weeks 4, 8, and 16 after randomization.

#### Adverse events

Any adverse events related to acupuncture will be monitored and recorded by participants or acupuncturists using a designed questionnaire. Possible adverse events are local bleeding, redness, itching at the sites of needle insertion, and dizziness throughout treatment. Adverse events will be assessed by outcome assessors weekly during the treatment period.

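### Adverse-event recording is limited to acupuncture-related events, with unblinded acupuncturists among the recorders, and stops at week 4 of 16, which could bias and does truncate the safety data

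*Protocol article*

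**What the plan says.** Four parts of the protocol article bear on this.

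- **Adverse events, what is recorded and by whom.** "Any adverse events related to acupuncture will be monitored and recorded by participants or acupuncturists using a designed questionnaire". The section then gives the events it expects: "Possible adverse events are local bleeding, redness, itching at the sites of needle insertion, and dizziness throughout treatment".
- **Adverse events, who assesses and when.** "Adverse events will be assessed by outcome assessors weekly during the treatment period".
- **Blinding.** "The acupuncturists who deliver the treatment to the participants will not be blind to treatment allocation". For everyone else: "Participants and all other investigators will be blinded to the treatment allocation, including the data analysis and outcome assessors".
- **Outcomes, Table 3.** The row labelled "Adverse events" sits in the secondary-outcome block. It has four marks, at weeks 1, 2, 3 and 4, and none at weeks 8, 12 or 16. Efficacy follow-up runs longer. Under Global assessment at other time-points, the responder rate "will also be measured weekly (during the treatment) and at weeks 8, 12, and 16 after randomization". Symptom scores follow the same schedule, and the quality-of-life index and the anxiety and depression scale are collected at weeks 8 and 16.

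**The concern.** The recording rule makes attribution to acupuncture the entry condition. Usual practice is the reverse: record the event first, then judge its cause. If the recorder decides that an event has nothing to do with the needles, the rule as written does not call for it to be recorded, and nobody can revisit that decision later.

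This matters more when the recorder knows the arm. The two treatments differ in ways the acupuncturist sees. Verum uses eight acupoints with manual stimulation to obtain De qi. The control uses six non-acupoints at 2 mm with no stimulation. The same episode of dizziness or abdominal discomfort might be put down to treatment more readily after the first than after the second.

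Separately, the schedule ends adverse-event collection when treatment ends, although participants are assessed three more times. A pilot meant to inform a larger trial would then have a safety record limited both in kind and in time.

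**Working it through.** **Step 1. Collection window.** Inputs: adverse-event marks at weeks 1 to 4 and last follow-up at week 16, both from Table 3. The text agrees, since assessment is weekly in the treatment period and treatment lasts four weeks.

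- Covered: 4/16 = 25%.
- Not covered: (16 − 4)/16 = 12/16 = 75%.
- Scheduled assessments with no adverse-event mark: weeks 8, 12 and 16, so three.

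**Step 2. Who handles an adverse event, and what each role is told to capture.**

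| Role | Task in the Adverse events section | Blinded? | Scope stated | Ends |
|---|---|---|---|---|
| Participant | Records on questionnaire | Yes | Acupuncture-related | Not stated; Table 3 ends at week 4 |
| Acupuncturist | Records on questionnaire | No | Acupuncture-related | Not stated; Table 3 ends at week 4 |
| Outcome assessor | Assesses weekly | Yes | Not qualified either way | End of treatment |

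No row of this table states all-cause collection, and none extends beyond week 4. Only the acupuncturist row is open to bias from knowing the allocation. The participant row keeps the causality filter without that bias. The assessor row may be broader, but the text does not say so, and it follows directly on a sentence confined to related events.

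**Step 3. How a filter could create a difference.** The document gives no event rates and no labelling rates, so this is an illustration with assumed inputs. Let *p* be the true event rate, the same in both arms. Let *s_V* and *s_M* be the shares of events labelled related, and so recorded, under verum and minimal acupuncture. The recorded rates are *p·s_V* and *p·s_M*, and the spurious difference is *p·(s_V − s_M)*.

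| *p* | *s_V* | *s_M* | Recorded, verum | Recorded, minimal | Spurious difference |
|---|---|---|---|---|---|
| 20% | 1.0 | 1.0 | 20% | 20% | 0 points |
| 20% | 0.9 | 0.6 | 18% | 12% | 6 points |
| 20% | 0.9 | 0.3 | 18% | 6% | 12 points |
| 10% | 0.9 | 0.6 to 0.3 | 9% | 6% to 3% | 3 to 6 points |
| 30% | 0.9 | 0.6 to 0.3 | 27% | 18% to 9% | 9 to 18 points |

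Equal labelling in both arms, at any level, gives zero. The illustration also lets every event pass through the differential filter. Events that reach the record through blinded participants or assessors would shrink the difference. It shows the mechanism and does not estimate its size in this trial.

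**Step 4. What is captured after week 4 by other means.** The global scale has three grades of worsening and runs to week 16. Eight dyspepsia symptoms, including nausea, vomiting and epigastric pain, are scored to week 16. The gap after week 4 therefore concerns events other than dyspepsia symptoms.

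**The case against.** The best reply is that blinded people already do much of the work. Outcome assessors review adverse events every week, the sentence that says so carries no relatedness qualifier, and one of the two recorders is the blinded participant. The expected events are acute and tied to needling, and all 12 sessions fall within the four weeks covered, so the window fits the harms the plan expects. The article also condenses a fuller protocol, where reporting of serious events and causality grading would normally be set out.

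Much of this stands, and it limits the point. A reader might infer any of the following, and the document supports none of them:

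- *That the safety comparison is biased, or rests on unblinded judgement alone.* The document does not say who decides relatedness or when. Blinded assessors and participants are both involved, and no specific between-arm safety test is named. Adverse events are listed among the secondary outcomes and categorical variables go to a chi-square test, so a comparison by arm is a natural use, but bias in it is possible, not shown.
- *That worsening of symptoms is lost.* The global scale and the symptom scores record it to week 16, though not as an adverse event.
- *That the monitoring board sees an incomplete record.* What the board receives is in an additional file that is not shown.
- *That the small arms measure the harm done.* Bounds or percentages derived from 21 per arm follow from the sample size and would be unchanged by better recording.

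Two things survive. The related-only rule and the week-4 end are stated in the article, so they are not gaps left by condensation. And the weekly blinded assessment answers them only in part, because it is not stated to elicit events of every cause and it also ends with treatment. That the expected events are acute is a good reason to ask weekly during treatment. It does not explain leaving out unexpected events at assessments that take place anyway.

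**Conclusion.** The point holds in a limited form. As written, recording is restricted to acupuncture-related events, unblinded acupuncturists are one of two recording sources, and collection ends at week 4. The filter could differ by arm and so could bias the comparison of adverse events. The direction and size of any bias cannot be determined from the document and would be zero if both arms were labelled alike. The truncation is definite: for events other than dyspepsia symptoms, 12 of 16 weeks (75%) have no planned collection. That percentage counts weeks without collection, not harms missed, and most needle-related events would be expected earlier. The conclusion assumes that the recording sentence and Table 3 mean what they say, and that the assessors' weekly task is no wider than its text. The primary efficacy outcome is unaffected. The change should be made because it is cheap and the pilot is meant to inform a larger trial.

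**What to change.** - Reword the recording rule so that every adverse event is recorded whatever its suspected cause, by whoever learns of it.
- State that the outcome assessors ask about all adverse events and grade relatedness after the event is recorded. They are already blinded. The description they grade should leave out the exact needle sites and manner of stimulation, because these differ between the arms.
- Report all-cause and related events separately by arm.
- Extend the adverse-event row of Table 3 to weeks 8, 12 and 16, at least for serious events and events leading to withdrawal.

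The cost is new wording on the case report form, one added question at three assessments already scheduled, and some grading time for the assessors. The downside is a few more minor, unrelated events to code. Since the trial is recruiting, the date of the change should be recorded, so that events collected under the old and new rules can be told apart.
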